### Details of analyses

#### a. Analysis methods overview

Our analysis follows the BEST-D data analysis plan and will carry out comparisons as intention-to-treat analyses. The main analyses at each stage are outlined below. Methods are intricate and evolving however and several stages are dependent on the particular characteristics and quality of the acquired measurements. Here we only provide a brief overview of the general steps that will be taken at each stage.

#### b. Data collection and management

All results will be handled according to the trial and institutional guidelines in secure servers within the University of Oxford in accordance with current regulations.

#### c. Data pre-processing, quality control and statistical analysis

Genome-wide genomic measurements involve hundreds of thousands of data points and typically require pre-processing and quality control (QC) analysis. These will be carried out according to published methods and current best practice. A brief description, including software to use in some instances, is provided below as guidance and to exemplify the planned approaches.

### *DNA extraction and genotyping*

Genome-wide genotyping and statistical methods of genetic association have become widely available, particularly over the last five years, and have proved highly reproducible (Visscher, Brown et al., 2012). We will adhere to current recommendations and best practice. The following general steps are required and are described in more detail elsewhere:

- 1) DNA extraction and genotyping as specified separately;
- 2) Quality control of subject and SNP genotyping data includes:
  - a. Gender misidentification;
  - b. Subject relatedness, duplication and divergent ancestry;
  - c. Individuals with elevated missing data rates or outlying heterozygosity rate;
  - d. Identification of markers (SNPs) with excessive missing data rates;
  - e. Identification of differing genotype call rates between groups;
  - f. SNP quality (filtering of monomorphic SNPs, SNPs with missing values or nonsense values; imputation quality; low call rate; violation of Hardy-Weinberg Equilibrium; duplication; and minimum allele frequency);
  - g. Association tests will be carried out as described previously (Sham and Purcell, 2014; Pirinen, Donnelly et al., 2013) using frequentist methods

(typically based on Chi-square tests) and allowing for multiple testing correction. We will consider Bayesian methods for specific instances, such as fine mapping, as previously described (Stahl, Wegmann et al., 2012; Stephens and Balding, 2009). Association tests will be carried out at the appropriate step for the particular analysis (e.g. during QTL analyses).

#### *Imputation of genotype data*

Genotype imputation is a computational method that can increase the power of genetic association studies (Marchini and Howie, 2010). It has been used commonly in genome-wide association studies to infer missing genotypes, fine-map associations and harmonise data sets (Porcu, Sanna et al., 2013). We plan to perform imputation and use data to fine-map significant associations. The following steps and tools are generally necessary during imputation:

- 1) Harmonisation of markers, reference panel and pre-imputation quality control;
- 2) Phasing of genotypes, imputation, post-imputation quality control.

#### *Microarray gene expression profiling*

Genome-wide gene expression profiling has become a common approach to interrogate cellular function and provide mechanistic insight. Microarray methods are available and in general statistical methods are mature and well accepted. Established protocols, statistical approaches and software are available for analysis of transcriptomic data that can also account for multifactor designed experiments. Simultaneous comparisons between many RNA targets with a variety of experimental conditions and predictors can be performed. Analytical workflows are generally intricate however and require normalisation; outlier analysis; adjustment for confounding effects; differential expression analysis, and integration with genotype, phenotype, external sources (e.g. gene annotations) or other available data. Analysis of differential expression generally relies on the use of linear models (Smyth, 2004) although Bayesian approaches can also be applied. We will include the following steps in our data analysis:

- 1) RNA extraction, cDNA conversion and microarray measurements as specified separately;
- 2) Normalization of microarray data, adjustment for confounding effects and differential expression analysis:
  - a. Quality assessment;
  - b. Pre-processing and probe filtering;
  - c. Control of possible confounding effects;
  - d. Differential expression analysis, uniquely expressed genes and downstream analysis.

#### *Expression quantitative trait loci (eQTL) analysis*

Several statistical models have been described for eQTL analysis (Battle and Montgomery, 2014; Montgomery and Dermitzakis, 2009). We plan to follow our published approaches (Fairfax 2012, 2014) including using an additive linear model as implemented in the R package MatrixEQTL (Shabalin, 2012) with inclusion as appropriate of covariates including dominant principal components of variance and comparing its reproducibility to other approaches such as an ANOVA model (Shabalin, 2012). Although our study is based on a randomised trial, we can

compare eQTL results for reproducibility while accounting for the effects of hidden factors (Gao, Tignor et al., 2014; Fusi, Stegle et al., 2012). We will investigate context-specificity for vitamin D supplementation using multivariate Bayesian (Petretto, Bottolo et al., 2010; Imholte, Scott-Boyer et al., 2013) and GWAS meta-analysis (hierarchical model) (Flutre, Wen et al., 2013) approaches. Once genotype and gene expression data have been processed as described above we will perform the eQTL analysis as mentioned including the following steps:

- 1) Probe filtering;
- 2) Confounding factors analysis;
- 3) Definition and identification of *cis* and *trans* SNPs;
- 4) Conditional analysis for fine mapping;
- 5) Quantification statistics.

#### *Functional annotation of eQTL signals and overlap with known associations*

Once we have a list of eQTL signals we will search public databases for other known associations and overlap with disease-associated variants to aid biological interpretation. The main studies and databases that we expect to use include ENCODE (Dunham, Kundaje et al., 2012), FANTOM5 (Andersson, Gebhard et al., 2014; Forrest, Kawaji et al., 2014), GTex (GTex Consortium, 2013), Epigenome roadmap (Bernstein, Stamatoyannopoulos et al., 2010), GWAS catalogue (Hindorff, Sethupathy et al., 2009), GWAS central (Beck, Hastings et al., 2014), amongst others. In the case of overlap with disease-variants we will use GWAS disease categories as described (Fairfax, Humburg et al., 2014). Enrichment of eQTLs in GWAS categories will be tested, for example using Fisher's exact test. Further enrichment analysis will also be carried out using GAT if appropriate (Heger, Webber et al., 2013). Background values will be those appropriate to the test (i.e. all SNPs) as will the comparison against expected values (i.e. all significant *cis*-SNPs). We will consider GWAS SNPs to overlap with significant eQTL SNPs if these are in high linkage disequilibrium ( $r^2 > 0.8$ ).

#### *Pathway, network and co-expression analyses*

Pathway analyses will be carried out with one or several packages, namely Ingenuity Pathway Analysis (IPA, Ingenuity Systems), in order to define gene networks, upstream regulators, and canonical pathways. Other database repositories and analysis tools such as DAVID (Huang da, Sherman et al., 2009) and GREAT (McLean, Bristor et al., 2010) will be used for comparison if necessary. We will perform gene co-expression network analysis using WGCNA (Langfelder and Horvath, 2008). If particular gene signatures are identified, we will make further comparisons against specific repositories. For example, if an interferon regulated pathway were identified, we will use published articles and databases such as: <http://interferome.its.monash.edu.au/interferome/home.jsp> (Rusinova, Forster et al., 2013). Significance thresholds will remain as those stated below after p-value adjustment where required (i.e. 1%, 5% and 10% values for interpretation, sensitivity and comparison with 5% as the accepted minimum threshold).

#### *Methods for handling missing data*

Pairwise deletion or multiple imputation of missing data as deemed appropriate for the particular analysis and variable will be used. For multiple imputation, results will be compared with those from complete-case analyses.

### *Allowance for multiplicity of comparisons*

We will use approaches based on false discovery rates and multiple-testing correction (such as Bonferroni and Benjamini-Hochberg methods), taking into account the type of measure and evidence from other studies as found relevant. We will aim to carry out permutation tests where appropriate.

### *Tests for heterogeneity effects*

For the main effects and comparisons (i.e. gene expression) we will carry out comparisons between sub-groups of participants to tests for heterogeneity with allowance for multiple comparisons and for other differences between the subgroups. We will use this to determine whether the effects in these subgroups are significantly different from the overall effect. Given the availability of genetic variation data and the study objective of identifying functional variants, the differences that we may observe could be due to a true biological effect as previously reported in other contexts (Lee, Ye et al., 2014; Fairfax, Humburg et al., 2014; Qiu, Rogers et al., 2014; Visscher, Brown et al., 2012).

### *Use of Bayesian and non-standard statistical techniques*

Current approaches in computational and statistical genomics largely apply frequentist methods. Although some of the analytical methods are mature, such as those for genetic association and gene expression, it remains a rapidly evolving field. We may compare methods and approaches where possible and appropriate to help determine sensitivity and reproducibility of findings.

### *Covariates*

Sex, age, body mass index, dietary calcium intake, prior history of disease (cardiovascular disease, cancer); total and differential blood cell count.

Possible batch and hidden effects, particularly in genotype and gene expression data, will be resolved using principal components analysis and accounted for. In gene expression analysis this is standard and sample randomisation for microarray measurements will be performed to minimise this.

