### Outcomes

- a. Primary outcomes
  - Genome-wide differential gene expression for peripheral blood leukocytes following vitamin D supplementation (profiling at baseline and 12 months, resolution of differentially expressed genes);
  - Genome-wide single nucleotide (SNP) genotyping of study cohort (baseline);
  - eQTL mapping of local (likely cis-acting) and distant (trans-acting) SNP markers associated with gene expression in different contexts of vitamin D supplementation.
- b. Secondary outcomes
  - Pathway and systems biology analysis of differentially expressed genes associated with vitamin D supplementation and co-expression gene modules;
  - Analysis of genotype-transcriptome-plasma 25(OH)D associations;
  - Analysis of quantitative trait loci (QTL) for plasma levels of 25(OH)D in BEST-D participants using genetic variants previously associated by genome-wide association studies (Wang, Zhang et al., 2010; Ahn, Yu et al., 2010);
  - Analysis of molecular associations between genotype, gene expression, plasma 25(OH)D and pre-specified plasma measurements (PTH, calcium, albumin, phosphate, creatinine, alkaline phosphatase, total cholesterol, LDL-C, HDL-C, triglycerides, apolipoprotein A, apolipoprotein B, hsCRP and NT-proBNP). These will be primarily carried out for concurrent measurements (i.e. for those at

baseline and 12 months). See also the protocol and data analysis plan for BEST-D;

- Analysis of the association between molecular measurements and pre-specified phenotype measurements including fractures, respiratory infections, body mass index, bone density measurements, glomerular filtration rate and urinary albumin/creatinine ratio;
  - Measurement of pro- and anti-inflammatory cytokines prioritised by the mRNA profiling described in the primary outcome.
- c. Tertiary outcomes
- Quantitative trait locus (QTL) analysis of pre-specified plasma measurements for those mentioned above;
  - Analysis of association of molecular and physiologic measures including systolic and diastolic blood pressure, heart rate, and arterial stiffness measured at 12 months;
  - Analysis of association of molecular and echocardiographic measures for a pre-specified sub-group at 12 months.

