### Comparisons

- a. Primary comparisons of the primary outcomes:
- All participants allocated 100 µg (4,000 IU) vitamin D3 daily (data collected at 12 months) vs. baseline;
  - All participants allocated 100 µg (4,000 IU) vitamin D3 daily vs. all participants allocated placebo.
  - All participants allocated 100 µg (4,000 IU) vitamin D3 daily vs. all participants allocated 50 µg (2,000 IU) vitamin D3 daily;
  - All participants allocated 50 µg (2,000 IU) vitamin D3 daily vs. baseline
  - All participants allocated 50 µg (2,000 IU) vitamin D3 daily vs. participants allocated placebo.
- b. Secondary comparisons of the primary outcomes:
- Participants allocated any active vitamin D3 dose (50 µg or 100 µg daily) versus participants allocated placebo.
- c. Tertiary comparison of the primary outcomes:
- All participants (4,000 IU, 2,000 IU and placebo) will be analysed according to treatment allocation separately using the following covariates (baseline characteristics):
- Sex
  - Age (<70, ≥70 years)
  - BMI (<25, ≥25 to <30, ≥30 kg/m^2)
  - Plasma 25(OH)D concentrations (<25, ≥25 to <50, ≥50 nmol/L)
  - Dietary calcium intake (<800, ≥800 to <1000, ≥1000 mg/day)
  - Estimated glomerular filtration rate (eGFR) (<60, ≥60 to <90, ≥90 ml/min/1.73 m^2)
  - Prior history of cardiovascular disease
  - Prior history of cancer

Although intervals have been assigned for some variables, continuous data will be used where appropriate. A generalized linear model for gene expression and

baseline characteristics will be used as part of this analysis as described in similar studies (Smyth, 2004) and specified below.

- d. Comparisons of secondary and tertiary outcomes will include:
- Changes from baseline within each treatment allocation;
  - Participants allocated 100 µg vitamin D3 daily vs. participants allocated placebo;
  - Participants allocated 50 µg vitamin D3 daily vs. participants allocated placebo;
  - Participants allocated any active vitamin D3 dose (50 µg or 100 µg daily) vs. participants allocated placebo;
  - In some instances, comparisons will be made between vitamin D3 dose groups to understand dose responses.

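### The covariate list omits season of blood draw, although the level of plasma 25(OH)D is the outcome of a QTL analysis: an avoidable loss of precision, not a bias

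*SAP*

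**What the plan says.** The Covariates section of the SAP gives the adjustment set as "Sex, age, body mass index, dietary calcium intake, prior history of disease (cardiovascular disease, cancer); total and differential blood cell count". It adds that "Possible batch and hidden effects, particularly in genotype and gene expression data, will be resolved using principal components analysis and accounted for". The list of baseline characteristics under Comparisons, part c, has no season or date of draw either, and neither appears elsewhere in the SAP as an adjustment or stratification factor.

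Plasma 25(OH)D enters the analyses in three ways:

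- As an outcome. A secondary outcome is the "Analysis of quantitative trait loci (QTL) for plasma levels of 25(OH)D in BEST-D participants using genetic variants previously associated by genome-wide association studies".
- In same-visit associations with genotype, expression and other plasma measurements. Of these the SAP says "These will be primarily carried out for concurrent measurements (i.e. for those at" baseline and 12 months.
- As a baseline characteristic in the tertiary comparison, in the classes "<25, ≥25 to <50, ≥50 nmol/L". The SAP qualifies these: "Although intervals have been assigned for some variables, continuous data will be used where appropriate".

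The Design section has 100 participants in each of three groups, with DNA and RNA samples at baseline and 12 months.

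**The concern.** Sampling twelve months apart puts both draws of one person at about the same time of year, so season largely cancels from within-person change. It does not cancel when the level at one visit is the outcome, as in the 25(OH)D QTL analysis. There, participants drawn at different times of year differ for a reason that is unrelated to genotype and that a known covariate could remove.

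The principal components do not clearly fill this gap. They are directed mainly at genotype and expression data, where many measured features allow hidden factors to be estimated. They are not a stated adjustment for a single plasma outcome.

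At stake is precision in a secondary analysis of at most 300 people, in which single variants may explain only a small share of the variance.

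**Working it through.** **No figure to reproduce.** The SAP gives no power calculation, effect size or SD for the 25(OH)D QTL analysis. The only input from the document is N = 3 × 100 = 300. That number applies at baseline, when nobody has yet been supplemented.

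**Assumptions, not in the SAP.** R² is the share of 25(OH)D variance explained by season, taken as 2% to 20%. For a cosine season with half-amplitude A and total SD 20 nmol/L, A = 20 × √(2R²), so this range corresponds to half-amplitudes of about 4.0 to 12.6 nmol/L.

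**Precision.** Genotype is unrelated to date of draw by design. Removing season therefore multiplies the standard error of the variant effect by √(1 − R²), and effective N = 300/(1 − R²).

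**Power illustration.** Take a variant explaining q = 2% of variance, tested at 0.05/4 = 0.0125 (four variants, also an assumption). The test is a 1-df F test with noncentrality 300q/(1 − q − R²). It runs from 6/0.98 = 6.12 without adjustment to 6/0.78 = 7.69 at R² = 20%. Residual df are 298 without season and 296 with it.

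| Season R² | SE multiplier | Effective N | Power |
|---|---|---|---|
| Season left in residual | 1 | 300 | 48.6% |
| 2% | 0.990 | 306 | 49.6% |
| 5% | 0.975 | 316 | 51.2% |
| 10% | 0.949 | 333 | 54.0% |
| 20% | 0.894 | 375 | 60.3% |

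**Placebo arm at 12 months.** With 100 people and the same R² range, effective N is 100/0.98 = 102 to 100/0.80 = 125. No gain has been worked out for the supplemented arms, where season should matter less.

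**Other amplitudes.** With within-season SD 18 and A = 5, 10 or 15 nmol/L, the seasonal share is (A²/2)/(A²/2 + 18²):

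- A = 5: 12.5/336.5 = 4%
- A = 10: 50/374 = 13%
- A = 15: 112.5/436.5 = 26%

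The answer is sensitive to the SD. With A = 10 and SD 25, the share is 50/675 = 7%.

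**Recruitment window.** The shares above assume enrolment spread over a full year. For full-year shares of 5% to 20%, shorter windows leave:

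| Window | Season R² within window | Effective N |
|---|---|---|
| 6 months around the trough | 1.0% to 4.5% | 303 to 314 |
| 3 months on the steep part of the curve | 1.9% to 8.3% | 306 to 327 |
| 3 months around the trough | 0.1% to 0.4% | 300 to 301 |

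**Baseline classes.** In simulation (mean 45 to 60, SD 20, full-year recruitment, season R² 5% to 20%), about 9% to 26% of people would fall in a different class if their values were standardised for season. This measures how far the classes depend on time of year. It is not an error rate, for the reason given under the objection.

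**The case against.** Four points can be made on the other side.

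1. *Season is an optional precision covariate.* Genotype has no designed link to month of draw, the analysis is secondary and the power gain is modest. This stands as a limit on weight. It does not remove the point: the SAP fixes a covariate list for these models, and a cheap term that bears on the outcome is left out.

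2. *The size is unknown.* The SAP gives no 25(OH)D distribution or recruitment calendar and does not say that 25(OH)D is seasonal. It also says that it follows the main BEST-D analysis plan, which is not at hand and may deal with season. This stands, and so the gain is shown only as a range that reaches nearly zero.

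3. *The baseline classes are not wrong.* A reader might infer that season misclassifies a quarter of participants and turns the comparison by baseline status into winter against summer. The SAP does not support that. The classes describe the measured concentration at the draw, and a low winter value is truly low when the RNA was taken. Season acts partly through 25(OH)D, so adjusting for it there could remove real exposure differences. The section on tests for heterogeneity also promises allowance for other differences between subgroups, although it does not name season.

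4. *Expression and eQTL models are already covered.* A reader might want season in those too. The Covariates and eQTL sections already plan for hidden factors there, and no gain has been shown. The same lack of a shown gain applies to PTH as an outcome.

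**Conclusion.** The point holds for models with plasma 25(OH)D as outcome, as a conditional and modest improvement. Season of draw is not listed, and neither the 12-month spacing nor the principal components take it out of a 25(OH)D level.

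The consequence is lost precision in the baseline and placebo-arm models. At baseline, adjustment would be worth 6 to 75 extra participants on 300, and 1 to 12 percentage points of power for the illustrative variant. This rests on an assumed seasonal share of 2% to 20% and on recruitment spread over much of the year. With a short window the gain all but disappears.

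The genotype effect and the randomised between-arm comparisons are not biased. For the comparison by baseline 25(OH)D, season as a primary adjustment is debatable.

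**What to change.** In the Covariates section, add season of draw, entered as sine and cosine of the calendar date of the sample, to models with plasma 25(OH)D as outcome. Include treatment allocation as well in the 12-month models. If recruitment was too short for this to matter, one sentence saying so would do instead.

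For the tertiary comparison by baseline 25(OH)D, use the continuous value, which the SAP already allows, and report one sensitivity analysis that adds season of draw.

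The cost is a change of SAP wording and two degrees of freedom per model, provided that sample dates were recorded. The SAP does not say whether they were.

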### *Pre-specified sub-group analysis*

- Individuals with particular genetic variants may show a different response to vitamin D3 supplementation. If these individuals are identified by eQTL mapping, we will carry out further analyses to try and gain further understanding of the mechanisms and possible consequences.
- We will carry out an analysis of molecular associations with echocardiographic data for the sub-group of individuals for whom these will be available.
- We will analyse separately individuals who present any adverse outcome.

### *Post-hoc analysis*

Functional genomics approaches typically make use of genome-wide strategies that assay many functions and relationships. The outcomes and comparisons described above may generate hypothesis that will require additional experimentation and analysis. They will also likely require validation and/or follow-up work. These analyses and further experiments cannot be specified *a priori* and may for example involve the measurement of other molecules, epigenetic marks, integration with other

molecular or phenotypic data, comparison with other cohorts and/or integration with other experiment models or other approaches as deemed appropriate.

